##### Numerical rating scale

2.7.2.5

During the trial, the NRS score of the more affected knee will be assessed at baseline and at weeks 4, 8, and 12. The primary analysis will focus on the change from baseline to week 8 to evaluate the treatment effect, while scores at other time points will be used to assess the trend and maintenance of efficacy.

##### Global pain scale

2.7.2.6

During the trial, the GPS score of the more affected knee will be assessed at baseline and at weeks 4, 8, and 12. The primary analysis will focus on the change from baseline to week 8 to evaluate the treatment effect, while scores at other time points will be used to assess the trend and maintenance of efficacy.

##### Lequesne functional index (Lequesne index)

2.7.2.7

During the trial, the Lequesne index score of the more affected knee will be assessed at baseline and at weeks 4, 8, and 12. The primary analysis will focus on the change from baseline to week 8 to evaluate the treatment effect, while scores at other time points will be used to assess the trend and maintenance of efficacy.

##### Knee injury and osteoarthritis outcome score

2.7.2.8

During the trial, the KOOS of the more affected knee will be assessed at baseline and at weeks 4, 8, and 12. The primary analysis will focus on the change from baseline to week 8 to evaluate the treatment effect, while scores at other time points will be used to assess the trend and maintenance of efficacy.

##### Short form 36 health survey (SF-36)

2.7.2.9

The SF-36 subscales of physical functioning, role physical, bodily pain, general health, vitality, social functioning, role emotional, and mental health, as well as the total score, of the more affected knee will be assessed at baseline and at weeks 4, 8, and 12. The primary analysis will focus on the change from baseline to week 8 to evaluate the treatment effect, while scores at other time points will be used to assess the trend and maintenance of efficacy.

### Adverse events

2.8

All trial investigators, responsible units, clinical monitors, and participants must record and promptly report any AEs to the project leader and study team, regardless of their relationship to the study intervention. AEs should be documented in the source documents and case report forms (CRFs), including a description of the event, onset time, duration, severity, frequency, interventions administered, outcome, and the investigator’s assessment of causality. Common AEs associated with acupuncture and electroacupuncture include fainting, needle retention, needle breakage, local pain, bleeding, or subcutaneous bruising, which are generally mild to moderate. Investigators should provide appropriate symptomatic management according to the participant’s condition and continue follow-up until the participant’s condition stabilizes. Relevant clinical data should be properly preserved to support AE evaluation and reporting.

### Serious adverse events

2.9

SAEs include events that lead to hospitalization, prolongation of hospitalization, persistent or significant functional impairment, are life-threatening, result in death, or are considered by medical judgment to require intervention to prevent the occurrence of the above serious outcomes. In the event of an SAE, the clinical physician must immediately (within 2 h) report it to the project leader and the study team. The study team shall report the SAE to the ethics committee and the sponsor within 24 h. The SAE must be recorded in detail in the CRF, including the time of occurrence, severity, outcome, causal relationship, reporting status, and management process. Appropriate management should be implemented according to the participant’s condition, and consultation with relevant departments or hospitalization may be arranged if necessary. If emergency unblinding is required to confirm the treatment received, the participant will be withdrawn from the trial and recorded as a dropout. The study team will continue to follow up until the participant’s condition stabilizes. All costs arising from the management of SAEs and AEs will be covered by the study-designated funding.

### Attendance and drop-out

2.10

Participants will be informed that they have the right to withdraw from the clinical trial at any time without obligation. The reasons for withdrawal will be tracked and recorded. Participants are not required to provide a reason for withdrawal; however, if the withdrawal is related to an AE, the investigator will take necessary measures based on the participant’s condition until it stabilizes. In the case of abnormal laboratory results, follow-up will continue until normalization is achieved. The method of follow-up, including hospitalization, outpatient visits, home visits, or telephone follow-up, will be determined based on the severity of the AE. Participants who receive other treatments or enroll in other clinical trials during the study will be considered as withdrawn from the trial.

### Data management

2.11

A dedicated database system for this trial will be developed using EpiData version 3.1 (EpiData Association, Denmark), based on the items in the CRFs. Logical checks and validation constraints will be incorporated during data entry. A trial run will be conducted to ensure the functionality and integrity of the system. Once the CRFs have been reviewed and signed, they will be submitted to the data manager, who will verify the data, including inclusion and exclusion criteria, dropout status, and missing values. If any inconsistencies or ambiguities are identified, a “data issue form” will be completed and returned to the clinical monitor for clarification. The investigator will provide written explanations, sign the form, and return it to the data manager. All data issue forms will be securely archived. Data entry will be performed using a double data entry method, in which two trained personnel independently enter the data. Discrepancies between entries will be resolved by comparing them against the original source documents and making necessary corrections.

All personnel involved in data management will receive training on the project background, CRF structure and coding, and data entry procedures. Data verification will be conducted using EpiData 3.1 by cross-checking each entry against the original CRF. To ensure data accuracy, random verification of 10 cases will be performed, comparing database entries with the corresponding CRFs to confirm consistency.

### Statistical analysis

2.12

Demographic Data Analysis: To assess the comparability between the three groups, demographic data and other baseline characteristics were compared. Continuous variables, such as age and Body Mass Index (BMI), were analyzed using independent-samples *t*-tests, provided that the data met the normality assumption. If the data did not meet the normality assumption, non-parametric tests, such as the Kruskal-Wallis test, were used. Categorical variables, such as gender, were analyzed using χ^2^ tests, ensuring that the assumptions for the test (e.g., adequate sample size in each category) were satisfied.

Clinical Efficacy Analysis: A multivariate analysis of covariance (ANCOVA) was performed to assess efficacy outcomes, with age, BMI, and disease duration included as covariates. The primary and secondary outcome measures were clearly defined, and potential confounding factors were controlled to ensure the robustness of the results.

Safety Analysis: The incidence of AEs and SAEs at 8 weeks post-randomization was compared across the three groups using χ^2^ tests. All AEs and SAEs were documented and analyzed to assess the safety of the interventions in each group.

Handling of Missing Data: After data collection is completed, the proportion, distribution, and possible mechanisms of missing data [e.g., missing completely at random (MCAR) or missing at random (MAR)] will be examined. For outcomes with a low proportion of missing data (≤5%) (36) and no apparent systematic pattern, complete-case analysis will be performed. If the proportion of missing data is higher or systematic missingness is observed, multiple imputation will be applied under the assumption of missing at random to reduce bias and maximize data utilization. Sensitivity analyses will be conducted to assess the robustness of the results under different missing data handling approaches. All analyses will be performed using R software (R version 4.4.3).

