Opposing needling, a classical technique involving contralateral acupoints with deep insertion along meridians, is primarily indicated for pain (21, 22) and has documented efficacy in various chronic pain disorders (23–27). From the perspective of traditional Chinese medicine, opposing needling emphasizes the concept of bodily integrity. When the flow of qi and blood along the meridians is obstructed and the left–right balance is disrupted, the meridian function on the affected side is weakened while the healthy side remains normal. Therefore, acupuncture at the corresponding points on the healthy side can stimulate the flow of qi, promote circulation of blood and qi, eliminate pathogenic factors, and restore the function of the affected meridians, achieving a dynamic balance of “yin and yang” between both sides of the body. From the perspective of modern medicine, studies have demonstrated that opposing needling can effectively relieve pain through protective inhibition of the cerebral cortex, reflex regulation via the nervous and humoral systems, and interruption of local nociceptive stimuli. The signals generated by acupuncture not only modulate pain transmission through spinal segmental connections but also promote the release of multiple endogenous analgesic substances, thereby increasing pain thresholds and activating descending inhibitory signals from higher centers. These combined effects contribute to the improvement of local pain and provide comprehensive pain management (28).

Previous studies suggest that opposing needling may enhance therapeutic outcomes in KOA, either alone or combined with other treatments (29–32). This indicates that opposing needling not only exerts an independent analgesic effect but may also play an adjunctive role. Therefore, we propose a reasonable hypothesis that combining opposing needling with electroacupuncture may produce additive or synergistic analgesic effects based on the analgesic action of electroacupuncture.

Given the independent and potential synergistic effects of opposing needling, we designed a sham-controlled, two-center randomized trial to evaluate the efficacy and safety of opposing needling as an adjunct to electroacupuncture in KOA patients. The study implements improved control procedures, comprehensive outcome measures, and refined group allocation to provide robust evidence and novel insights for clinical management.

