### Sample size

2.3

The sample size was estimated based on preliminary data (33, 34). The mean and standard deviation (SD) of the change in total WOMAC score after 8 weeks of treatment were assumed to be −32.3 ± 1.15 in the opposing needling plus electroacupuncture group, −22.42 ± 2.32 in the sham opposing needling plus electroacupuncture group, and −8.87 ± 0.81 in the conventional electroacupuncture group. The test power (1 − *β*) was set at 0.9, and the significance level (*α*) was set at 0.05. Based on these parameters, 30 participants were required per group. Considering a 20% dropout rate, the final sample size was determined to be 36 participants per group, resulting in a total of 108 participants.

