## Discussion

3

The present study is expected to provide robust evidence regarding the efficacy and safety of combining opposing needling with electroacupuncture for KOA. By testing the hypothesis that this combination may produce additive or synergistic analgesic effects, the trial aims to elucidate the therapeutic value of integrating these two classical acupuncture techniques. A rigorous three-arm parallel-group design will be employed, including an OE group, a SE group, and an EA group. On one hand, this design allows for the evaluation of the additive effect of opposing needling as well as the overall therapeutic benefit of the combined intervention; on the other hand, both the OE and SE groups receive bilateral needling, which helps reduce the risk of unblinding. In addition, the trial incorporates a comprehensive set of outcome measures, enabling a multidimensional assessment of the therapeutic effects of opposing needling plus electroacupuncture. Finally, the study emphasizes standardization and reproducibility of the intervention: all treatments will be administered by uniformly trained acupuncturists, and quality control and monitoring procedures are established to ensure intervention consistency and internal validity of the results.

Nevertheless, certain limitations remain. The follow-up period is limited to 12 weeks, allowing only preliminary evaluation of efficacy and precluding assessment of long-term effects in KOA; future studies should consider extending the follow-up duration. In addition, this is a two-center study with a relatively small sample size. Larger and multicenter RCTs will be required to further validate the generalizability and external applicability of the findings.

Overall, the results of this study are expected to strengthen the clinical evidence for acupuncture-based management of KOA, inform treatment optimization, and provide a foundation for future research on innovative needling techniques in chronic pain management.

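### No comparison is named as primary or as the one powered, so the efficacy result is not tied to opposing needling versus sham (OE versus SE)

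*Protocol article*

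**What the plan says.** The Introduction gives the aim of a sham-controlled trial "to evaluate the efficacy and safety of opposing needling as an adjunct to electroacupuncture in KOA patients". Section 2.7.1 fixes the primary outcome as WOMAC for the more affected knee and focuses the primary analysis on change from baseline to week 8.

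Section 2.12 describes the efficacy analysis in one sentence: "A multivariate analysis of covariance (ANCOVA) was performed to assess efficacy outcomes", adjusted for age, BMI and disease duration. It names no contrast between arms, no order of testing and no criterion for success.

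Section 2.3 lists an assumed mean change for each of the three arms. Power "was set at 0.9, and the significance level" "was set at 0.05. Based on these parameters, 30 participants were required per group". It does not say which comparison these figures refer to, or whether the test is one- or two-sided.

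The Discussion assigns the design two purposes, the additive effect of opposing needling and the overall benefit of the combination, and ranks neither. It also states the hypothesis: "By testing the hypothesis that this combination may produce additive or synergistic analgesic effects".

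**The concern.** Only OE versus SE uses the sham, so only that contrast separates opposing needling from the extra contact and expectation that come with needling the second leg. The article does not tie its efficacy conclusion to it. An overall three-arm test, or OE versus EA, could be reported as the result and still be silent on whether opposing needling does anything beyond sham.

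The plan's own assumptions make this a practical matter. They put SE 13.55 points better than EA, so more than half of the expected OE–EA difference already appears with sham. EA participants are needled on one side only (section 2.6.3), while the Discussion credits bilateral needling in OE and SE with lowering the risk of unblinding. A result carried by EA lacks that protection, and the outcome is a symptom score.

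The hypothesis raises a related difficulty. Telling synergy from additivity requires the effect of opposing needling in the absence of electroacupuncture, and all three arms receive electroacupuncture.

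**Working it through.** **Inputs.** From section 2.3: mean changes OE −32.3 (SD 1.15), SE −22.42 (SD 2.32), EA −8.87 (SD 0.81); 30 evaluable per arm; α = 0.05; power 0.9. Assumed here: common SDs of 10, 15, 20 and 25, two-sided tests, covariates ignored.

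**1. Can the powered comparison be inferred from the stated 30 per group?** Use n = 2(1.960 + 1.282)²·SD²/δ² per arm, with SD the root mean square of the two arm SDs.
- OE–SE: δ = 9.88, SD = 1.83, so n = 2 × 10.51 × 3.35/97.6 = 0.72, which rounds up to 1.
- OE–EA (δ = 23.43) and SE–EA (δ = 13.55) also give 1.
- Exact t calculations give 3, 2 and 2. A three-group ANOVA gives 2.

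No comparison reproduces 30. Solving backwards, 30 per arm at 90% power needs an SD of about 11.8 for OE–SE, 16.2 for SE–EA, 28.0 for OE–EA or 25.2 for the overall test. The sample size therefore does not reveal which comparison was intended.

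**2. How much of the expected OE–EA difference appears with sham?** 13.55/23.43 = 58%. The remaining 9.88 is OE–SE.

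**3. Overall test when opposing needling equals sham.** Set OE = SE = −22.42 and EA = −8.87. The sum of squared deviations from the grand mean is (2/3) × 13.55² = 122.4. Noncentrality λ = 30 × 122.4/SD², with F on 2 and 87 degrees of freedom (critical value 3.10). OE–SE is then a true null, rejected at its nominal level.

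| Assumed SD | λ | P(overall test significant) | P(OE–SE significant) |
|---|---|---|---|
| 10 | 36.7 | 1.00 | about 0.05 |
| 15 | 16.3 | 0.95 | about 0.05 |
| 20 | 9.2 | 0.76 | about 0.05 |
| 25 | 5.9 | 0.56 | about 0.05 |

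At the stated SDs the overall test rejects with probability about 1.00. In the same scenario OE versus EA is significant in about 93% of trials at SD 15 and 74% at SD 20.

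**4. Power if OE–SE is primary.** With δ = 9.88 and 30 per arm, the t-test noncentrality is 9.88/(SD × √(2/30)), which is 3.83, 2.55, 1.91 and 1.53 at SD 10, 15, 20 and 25. Power is about 97%, 71%, 47% and 33%.

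**5. Synergy.** The arms are EA, EA + sham and EA + opposing needling. An interaction needs four cells (neither, each alone, both). The cells without electroacupuncture are absent, so the data give only the effect of adding opposing needling to electroacupuncture.

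**The case against.** The strongest reply is that this is a condensed article. Contrasts, testing order and multiplicity rules are usually placed in an analysis plan, which is not shown, and the article does fix endpoint, knee and time point. That stands for the detail of a testing procedure. It does not cover which question is primary or which comparison was powered. Those belong to the design, and the article has its own sample size and analysis sections that leave both open, plus a Discussion naming two unranked purposes.

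A reader might infer several stronger points that the documents do not support:
- **That the plan will count an overall test or any significant pairwise test as success.** No success rule is stated. Even the three-level group factor is inferred from the design. The risk is what the text allows.
- **That EA alone drives the overall test.** Under the planning means (grand mean −21.20) the squared deviations are 123.3 for OE, 1.5 for SE and 151.9 for EA, so OE supplies about 45% and EA about 55% of the between-group signal. EA stands alone only in the OE = SE scenario.
- **That family-wise error is about 12%.** That figure applies to three unadjusted, ungated pairwise tests, which the plan does not state. Pairwise tests done only after a significant overall test hold it at about 5%.
- **That several outcomes are tested jointly.** The abbreviation is ANCOVA and three covariates follow, so the wording most likely means several covariates.
- **That the hypothesis is wholly untestable.** An add-on effect can be estimated; only synergy cannot be separated out.

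**Conclusion.** The point holds in limited form: the primary and powered comparison is unnamed, and the efficacy conclusion is therefore not bound to OE versus SE. If an overall test were taken as the result, the chance of a positive finding with no benefit over sham would be 56% to 100% for SDs from 25 down to 10, against about 5% for OE versus SE. These figures rest on the plan's EA and SE means, 30 evaluable per arm, no covariate adjustment and assumed SDs; the stated SDs cannot yield the stated sample size. The synergy claim goes beyond what the three arms can show. The defect is the unnamed contrast, not a demonstrated inflation of type I error.

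**What to change.** In section 2.12, name OE versus SE on change in WOMAC total at week 8 as the single primary contrast, from a univariate ANCOVA with the listed covariates, at two-sided 0.05. Test OE versus EA at 0.05 only if the first test is significant, and report SE versus EA descriptively. Replace the word multivariate accordingly. In section 2.3, say that the power statement refers to OE versus SE and give a justified SD for it. In the Introduction and Discussion, restate the hypothesis as an add-on effect of opposing needling. Make these changes before any unblinded data are seen.

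The text change is a few sentences, and the key contrast keeps the full 0.05. Other orderings would also be valid, but this one matches the stated aim. There are two costs. OE versus EA becomes conditional on the first test. Stating the powered comparison also exposes its power: 30 per arm gives 90% for the planned 9.88-point difference only if the SD is about 11.8 or less, and about 71% or 47% at SD 15 or 20, so the sample size may need revisiting.

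### Under the plan's own unequal planning SDs, pairwise contrasts from a pooled-variance three-arm ANCOVA would be miscalibrated; section 2.12 should name standard errors that allow unequal arm variances

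*Protocol article*

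**What the plan says.** Section 2.12 (Statistical analysis) names a single efficacy method: "A multivariate analysis of covariance (ANCOVA) was performed to assess efficacy outcomes, with age, BMI, and disease duration included as covariates". It attaches assumption conditions to the baseline comparisons (normality, adequate cell counts) but none to this model. It does not say which between-arm contrasts are taken, what error-variance structure is used or how standard errors are computed.

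Section 2.7.1.1 makes the change in WOMAC from baseline to week 8 the focus of the primary analysis. Section 2.3 (Sample size) gives the only figures on the variability of that change: an SD of "1.15 in the opposing needling plus electroacupuncture group", then a change of minus "22.42 ± 2.32 in the sham opposing needling plus electroacupuncture group" and of minus "8.87 ± 0.81 in the conventional electroacupuncture group". These are planning values: "The sample size was estimated based on preliminary data (33, 34"). Section 2.4 allocates 1:1:1.

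**The concern.** In its ordinary meaning, and in a default R fit, an ANCOVA with three arms estimates one common residual variance and uses it for every contrast between arms. The planning SDs for the same endpoint do not fit that assumption: 2.32/0.81 = 2.86, a variance ratio of 8.2.

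Equal arm sizes protect a two-arm comparison from unequal variances. They do not protect a pairwise contrast taken from a three-arm model, because the third arm also feeds the error term. The low-variance EA arm would make the OE versus SE standard error too small, and the high-variance SE arm would make the OE versus EA standard error too large. OE versus SE is the comparison that separates contralateral needling from its sham, and there the distortion would run towards false positives.

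**Working it through.** **The plan's own figure.** Section 2.3 states 30 per group at power 0.9 and alpha 0.05 (taken as two-sided; the article does not say). For OE versus SE the difference is 32.3 − 22.42 = 9.88 and the mean of the two variances is (1.15² + 2.32²)/2 = 3.352. The normal approximation gives n = 2 × 3.352 × (1.96 + 1.2816)² / 9.88² = 0.72, so 1 per group; using 2.32 as the SD gives 2. A one-way ANOVA exceeds 0.999 power at 2 per group. The stated 30 is not reproduced. At 30 per group and 90% power, a difference of 9.88 corresponds to an SD of 9.88 / [√(2/30) × 3.2415] = 11.8. The printed SDs are therefore doubtful in size, and what follows is conditional on them or on their ratio.

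**Pooled variance.** With equal arms, (1.3225 + 5.3824 + 0.6561)/3 = 2.454, a pooled SD of 1.566. The model variance of any pairwise contrast is then 2 × 2.454 = 4.907 (divided by n). The true variance is the sum of the two arms' own variances (divided by n).

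**Calibration.** Ratio of model to true standard error = √(4.907 / true variance). Type I error = 2 × [1 − Φ(1.96 × ratio)].

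| Contrast | True variance × n | Ratio | Type I error |
|---|---|---|---|
| OE vs SE | 1.3225 + 5.3824 = 6.705 | 0.856 | 9.4% |
| SE vs EA | 5.3824 + 0.6561 = 6.039 | 0.901 | 7.7% |
| OE vs EA | 1.3225 + 0.6561 = 1.979 | 1.575 | 0.2% |

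The OE versus EA interval is thus about 57% too wide, and the nominal 95% interval for OE versus SE covers 90.6%.

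**Simulation.** A three-arm ANCOVA with three covariates unrelated to outcome (20,000 trials, at 30 and at 36 per arm) gave type I error of 9.2% to 9.3% for OE versus SE, 7.2% to 8.0% for SE versus EA and 0.3% to 0.4% for OE versus EA. The omnibus three-arm F test ran at 6.1% to 6.3%. The calculation assumes that the SD ratio after covariate adjustment is close to the raw ratio.

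**Milder ratios** (OE:SE:EA = 1:r:1). The ratio of standard errors is √[2(2 + r²)/3 ÷ (1 + r²)].

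- r = 1.25: √(2.375/2.5625) = 0.963, type I error for OE versus SE 5.9%
- r = 1.5: √(2.833/3.25) = 0.934, 6.7%
- r = 2: √(4/5) = 0.894, 8.0%

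**Alternatives under the section 2.3 SDs.** HC3 standard errors in the same three-arm model gave 4.6% to 4.7% for OE versus SE, 3.7% to 4.0% for OE versus EA and 4.5% to 4.9% for SE versus EA. A pooled t-test on OE and SE alone, at equal n, gave 5.1%. With truly equal variances, HC3 standard errors averaged 1.028 times the ordinary ones at 36 per arm (10,000 trials).

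**The case against.** The strongest reply is that section 2.12 does not commit to the arrangement that produces these figures. It names an ANCOVA but no contrasts, variance structure or standard-error estimator, and an article may leave these to an analysis plan. If OE and SE were fitted as a pair, the test would run near 5%. This stands, and it makes the figures conditional. It does not remove the point: pooling over three arms is what the named method does by default, and it sits badly with the only variability the document states.

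Second, the SDs are weak evidence about the trial. They fail the plan's own sample-size calculation and rest on two references, without saying which arm came from which. This also stands. If the figures are standard errors from samples of equal size, the ratio and the result are unchanged, because a common factor cancels; but no source sample sizes are given, so that is an assumption.

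Third, under the plan's own effects no conclusion would change. At 36 per arm, OE versus SE gives z = 9.88 / (1.566 × √(2/36)) = 26.8 with the pooled standard error and 9.88 / √(6.705/36) = 22.9 with the correct one. That is right, but type I error and coverage matter when the true effect is small or the SDs are larger than printed.

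A reader might also infer that OE versus SE is the designated primary contrast. The article fixes the primary endpoint and time point but designates no contrast.

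**Conclusion.** The point holds as a conditional one. If the section 2.3 SDs or their ratio apply, and pairwise contrasts are taken from the three-arm ANCOVA with model-based standard errors, type I error would be about 9% for OE versus SE and about 8% for SE versus EA, and the OE versus EA interval would be about 57% too wide. At SD ratios of 1:1.25:1 to 1:2:1, the OE versus SE figure falls to about 6% to 8%.

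A reader might infer that the planned ANCOVA is invalid, or that the trial will test OE versus SE at 9%. The documents support neither: the SDs are planning values that may be mis-entered, and the contrasts and standard errors are not fixed. The arithmetic is firm; the prediction about the trial's actual variances is not. What remains is a cheap safeguard worth adopting.

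**What to change.** Add one sentence to section 2.12: the between-arm contrasts from the efficacy ANCOVA (OE versus SE, OE versus EA) use standard errors that do not assume equal variances across arms. Either HC3 robust standard errors or a model with arm-specific residual variances (for example gls with varIdent by arm) will do; both are available in R, the software already planned. Name one of them in advance, so that the choice is not made after seeing the data, and apply it to the secondary scores as well.

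The cost is one sentence and about one line of code, plus standard errors about 3% larger with HC3 at 36 per arm if the arm variances prove equal. The SDs in section 2.3 should be checked against their sources at the same time, since they and the 30 per group cannot both be right.

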### Randomization

2.4

Eligible participants will be randomly assigned in a 1:1:1 ratio to the opposing needling plus electroacupuncture (OE) group, sham opposing needling plus electroacupuncture (SE) group, or electroacupuncture alone (EA) group, according to the order of enrollment. The randomization sequence will be generated by an independent third party not involved in this study using SAS 9.4, with a stratified randomization method; the stratification factor is study center, and the block size is 6. Group allocation will be concealed in sequentially numbered, opaque, sealed envelopes. The envelopes will be opened by the acupuncturist immediately before the first treatment to determine group assignment.

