##### The Chinese version of the Western Ontario and McMaster universities osteoarthritis index (WOMAC) score for the more affected knee

2.7.1.1

During the trial, the WOMAC score of the more affected knee will be assessed at baseline and at weeks 4, 8, and 12. The primary analysis will focus on the change from baseline to week 8 to evaluate the treatment effect, while scores at other time points will be used to assess the trend and maintenance of efficacy.

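### The stated efficacy ANCOVA omits the baseline value of the outcome and the stratification factor centre; this costs precision but does not bias the effect on average

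*Protocol article*

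**What the plan says.** - **Efficacy model (section 2.12, Statistical analysis).** "A multivariate analysis of covariance (ANCOVA) was performed to assess efficacy outcomes", "with age, BMI, and disease duration included as covariates". No section of the article names the baseline score of any outcome, or centre, as a model term.
- **Primary endpoint (section 2.7.1.1).** "The primary analysis will focus on the change from baseline to week 8 to evaluate the treatment effect". The baseline score is available for everyone assessed: "the WOMAC score of the more affected knee will be assessed at baseline and at weeks 4, 8, and 12".
- **Randomisation (section 2.4).** "Eligible participants will be randomly assigned in a 1:1:1 ratio" to three arms, and "the stratification factor is study center, and the block size is 6". There are two centres.
- **Use of baseline data (section 2.6.7).** Baseline data are said to serve adjustment for confounding in general terms. The items listed there are disease duration, affected knee, radiographic grade, prior treatment and concomitant disease. Neither baseline WOMAC nor centre is among them.
- **Baseline comparability of the three groups (section 2.12).** Continuous variables "were analyzed using independent-samples *t*-tests, provided that the data met the normality assumption", with the Kruskal-Wallis test as the fallback.

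**The concern.** When the endpoint is a change score, the baseline value of the same score is the natural first covariate. Here it enters only by subtraction. That amounts to fixing the slope of week-8 WOMAC on baseline WOMAC at 1 instead of estimating it. If the true slope is below 1, the change score over-corrects: an arm that starts higher by chance appears to improve more.

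Centre raises a different issue. Stratifying by centre balances the arms within centre, so any centre difference in outcome cancels from the treatment contrast. A model without centre still counts that difference as residual noise, so its standard error is too large.

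At stake are the precision of the primary comparison in a trial that the Discussion itself describes as relatively small, and protection against chance imbalance with 36 patients per arm. The article states its own covariate list, so this is more than detail left to an analysis plan.

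**Working it through.** The plan gives no figure for the gain from adjustment, so there is none to reproduce. All correlations, SD ratios and centre effects below are assumptions.

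**1. Gain from baseline adjustment.** Let the week-8 SD be 1, the baseline SD be k, and their correlation be ρ.

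- Variance of the change score: 1 + k² − 2ρk.
- Residual variance after adjusting for baseline: 1 − ρ².
- The first minus the second is (k − ρ)², which is never negative. In large samples adjustment cannot lose precision, and it gains nothing only when ρ = k.
- Variance ratio, adjusted to unadjusted: (1 − ρ²) / (1 + k² − 2ρk). At k = 1 this reduces to (1 + ρ)/2.

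| ρ | k = 1 | Reduction | k = 0.7 | Reduction |
|---|---|---|---|---|
| 0.3 | 1.30/2 = 0.65 | 35% | 0.91/1.07 = 0.85 | 15% |
| 0.5 | 1.50/2 = 0.75 | 25% | 0.75/0.79 = 0.95 | 5% |
| 0.7 | 1.70/2 = 0.85 | 15% | 0.51/0.51 = 1.00 | 0% |

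The case k = 0.7 is included because section 2.2.3 requires an NRS pain score of at least 4 and Kellgren-Lawrence grade II or III, which may narrow the spread at baseline. The table ignores whatever age, BMI and disease duration already explain.

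**2. Chance imbalance.** With 36 per arm, the standard error of a baseline difference between two arms is √(2/36) = 0.24 baseline SD. An imbalance of that size shifts an unadjusted change-score contrast by (1 − slope) times the imbalance. At k = 1 and ρ = 0.5 the slope is 0.5, so the shift is 0.5 × 0.24 = 0.12 SD. At k = ρ = 0.7 the slope is 1 and the shift is zero.

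**3. Centre.** If centre explains a share R² of outcome variance and the arms are balanced within centre, leaving it out inflates the standard error by 1/√(1 − R²). This is 1.026 at R² = 0.05 and 1.054 at R² = 0.10. A simulation of the three-arm design (36 per arm, two equal centres, 20,000 runs, two-sided 5% test of one arm contrast) gave:

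| Share explained by centre | Size without centre | Size with centre |
|---|---|---|
| 0 | 5.1% | 5.1% |
| 5% | 4.3% | 4.9% |
| 10% | 3.9% | 4.9% |
| 20% | 2.8% | 5.2% |

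The error is in the conservative direction.

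**4. Baseline tests.** A t-test compares two groups, while its stated fallback, Kruskal-Wallis, handles three or more. If the t-tests were run as three uncorrected pairwise tests per variable, the chance of at least one false positive would be about 12.4% by simulation (1 − 0.95³ = 14.3% if they were independent), against 5% for one-way ANOVA. The article does not say that they would be run this way.

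**The case against.** Several stronger readings are tempting, and the documents do not support them.

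- **The treatment effect is biased.** A reader might infer that regression to the mean contaminates the comparison. Under randomisation it is expected equally in every arm, so the estimate is unbiased on average. What remains is the conditional shift when baselines happen to differ.
- **The covariate list is closed.** Section 2.12 does not say that only these three are used, and it adds that potential confounders are controlled. That does not cure the omission, because neither that sentence nor section 2.6.7 names baseline WOMAC or centre. The fair statement is that the stated list omits them.
- **The gain is a fixed number of patients or power points.** At k = 1 and ρ = 0.5, 108 adjusted patients carry the information of 108/0.75 = 144 unadjusted ones, but that is one point on a range reaching down to no gain. A power figure would need a usable SD. Section 2.3 prints 1.15, 2.32 and 0.81, with which pairwise formulas give only 1 to 2 patients per arm. An SD back-calculated from the stated 30 per group is about 11.8, 10.4 or 25, depending on the formula. That mismatch is a separate matter, and no power claim is made here.
- **The baseline t-tests threaten the efficacy result.** The efficacy covariates are named in advance, and nothing makes them depend on baseline tests. The t-test error affects only the description of the groups.
- **The primary analysis is a joint model of several outcomes.** *Multivariate* could be read so, but the article abbreviates the method as ANCOVA and defines one primary score. It is a slip of terminology.

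The objection therefore limits the size and kind of harm. It does not restore the missing terms.

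**Conclusion.** The point holds as one of precision and good practice, and the sponsor should act on it. The stated efficacy model lacks the outcome's baseline value and the only stratification factor, although both are already in hand. The text is clear, but the magnitude is not. The loss from omitting baseline runs from nothing to about a third of the variance over the assumed range (ρ 0.3 to 0.7, SD ratio 0.7 to 1). Omitting centre widens the standard error by about 3% to 5%, and lowers the actual size to about 4.3% to 3.9%, if centre explains an assumed 5% to 10% of variance. Neither omission raises the false-positive rate or biases the effect on average. The t-test and *multivariate* wording are minor corrections that change no efficacy conclusion.

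**What to change.** In section 2.12, specify for the primary endpoint an ANCOVA of week-8 change in WOMAC total on treatment group, baseline WOMAC total and centre, keeping age, BMI and disease duration. For each secondary outcome, use the same form with that outcome's own baseline value and centre. Delete *multivariate*. Replace the baseline t-tests with descriptive tables, or with one-way ANOVA if a test is wanted.

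The cost is wording and two model degrees of freedom, one for baseline and one for two centres. With 108 analysed, residual degrees of freedom go from 102 (intercept, two treatment terms and three covariates) to 100. No new data are needed. The change should be fixed before unblinded data are seen, so that the added covariates cannot be taken for a data-driven choice.
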